**Fig 1 pone.0326363.g001:**
[figure not shown]
SPIRIT Checklist for schedule of enrolment, interventions and assessments.

### Setting

The CHWS commenced operating on March 1 2024 from a community centre in Frankston (Melbourne, Australia) as an outpatient service, with opportunities for in-person and/or online assessments and interventions. During the establishment of the CHWS, staff completed a training program that included: (1) an overview of the CHWS operations and procedures (described below); (2) induction training required for new staff at Peninsula Health (the health service through which the CHWS was established); (3) training regarding all CHWS assessment procedures. One of the primary tools being used to guide discussion and prioritisation of carer needs at the initial CHWS assessment is the Carer Support Assessment Needs Tool (CSNAT) [31]. Staff have undertaken the required online training program for the use of the CSNAT before the Service commenced operations (https://csnat.org/). Licencing permission for use of the CSNAT, according to the authors’ defined terms of use has been received for this project (https://csnat.org/licensing/); (4) training for staff to support capacity building for carers in problem-solving for current and future potential problems associated with the carer role (based on a training program for a previous intervention trial for carers of older people being discharged from hospital) [32]; and (5) research data management. The training program included face-to-face (1–2 days) and online components.

### Staff governance

CHWS staff are employed through Peninsula Health. Operational governance (e.g., induction and orientation to employment, payroll, etc) is being overseen by Peninsula Health. Discipline-specific clinical supervision for each of the CHWS clinicians is provided through Peninsula Health staff and their existing supervision support pathways. Research and other clinical governance (e.g., training associated with various assessment tools, research requirements of the Carer Service, research skills, etc) are being overseen by the research team at Monash University.

### Ethics

The project has received approval from the Peninsula Health Research Ethics Committee (LNR99736PH-2023) and reciprocal ethical approval from the Monash University Health Research Ethics Committee (2023-40977-100362).

### Participants and recruitment

Participants include (1) older carers of older people (termed “carers” from this point); (2) referrers to CHWS; and (3) CHWS staff.

#### Carers.

Carers are defined as “family members and/or friends who routinely support the older person through assistance with household tasks; self-care and mobility; emotional and social support; treatments, medication and responding to acute health needs; advocacy and care coordination; or surrogate decision-making” [33]. The inclusion criteria for carers attending the CHWS, and for this study are (a) being aged ≥50 years; (b) living in the community; and (c) being an informal (unpaid) carer (as defined above) for a person aged ≥65 years living in the community.

Carers can be referred to the CHWS through referrals (e.g., general practitioners, allied health professionals, geriatrics services and specialist clinics, community health centres, and community aged care organisations) or be self-referred (e.g., through hearing about the CHWS from peers, media, or other avenues of service promotion). During initial contact with the CHWS, carers will be asked if they are willing to provide written informed consent to participate in the research evaluation of the CHWS. Whether or not the carer consents to participate in the research study, all carers will receive the same service provision through the CHWS. However, only those consenting to participate in the research will have their data included in the evaluation of the service.

During an initial phone contact, a CHWS staff member will complete a screening demographic questionnaire with the carer to ensure they meet the study inclusion criteria. Once eligibility and interest in participation in the study are determined, the carer will be asked to review the explanatory statement and consent form, and if willing to participate in the research, to sign the consent form and return it to the CHWS staff. CHWS staff will then inform the research team of carers who have agreed to participate in the research. Involvement in the research study will include allowing data from baseline and 6 month follow-up assessments to be used to evaluate the service outcomes and possibly being asked to be involved in a semi-structured interview after the 6 month assessment (which will involve a separate explanatory and consent form). Participants will be purposefully sampled for these interviews, aiming for diversity of age, years in the carer role, nature of prioritised needs, and health status of the carer. Carers who would like to find out more about the study before consenting to participate will be able to follow up with the CHWS staff member, or members of the research team.

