a)*Reach* will be determined through referrals received, aiming for >80% of appointment slots for all CHWS staff being utilised in the last six months of the study recruitment period; and overall sample size relative to the planned sample size (see analysis and sample size calculation section). Sources of referrals (medical practitioners, allied health professionals, carers themselves) will be reported;b)*Effectiveness* outcomes will mainly include the carer outcome measures (Table 1), and also a *cost-effectiveness* evaluation. A cost-utility analysis will be conducted using a societal perspective over a 12 month time horizon (6 months before the carer’s first appointment and 6 months following the carer’s first appointment). Cost data will include CHWS intervention costs (excluding research costs); carer emergency department presentations and hospital admissions (self-report); the quantity of care provided to the person requiring care, including average weekly hours of care provided by the carer, by other people who are not paid, and by other people who are paid (self-report). In addition, the carer will report the “preferred” and “actual” weekly hours spent on their top three leisure activities (noting when the carer role contributes to the gap between “preferred” and “actual” hours of participation). Effect data will be based on the utility index derived from the EQ-5D-5L [37], measured during the carer’s initial appointment and again at their 6 month follow-up assessment. The change in utility index between initial assessment and 6 months will be used to determine quality-adjusted life years (QALYs) gained or lost by the carer. Cost and effect data will be combined to determine incremental cost-effectiveness ratio (ICER) per QALY gained, with a threshold of <$AUD50,000/QALY gained to determine cost-effectiveness [55].c)*Adoption* will be evaluated through several service system outcomes (percentage completing intervention programs and 6 month assessment, number of interventions undertaken, and number of intervention sessions undertaken with CHWS staff). Acceptability of the service will be evaluated through the CAQ-8 and associated survey items, and interviews of a purposive sampling of carers (after the 6 month assessment), service referrers, and an interview with consenting CHWS staff in the last six months of the intervention, or an exit interview for staff leaving the service;d)*Implementation* includes fidelity of the program as intended (which will be evaluated by members of the research team reviewing 5% of de-identified patients’ assessments and intervention programs implemented against CHWS protocol) and adaptations (CHWS staff will document issues and adaptations made during the CHWS implementation and report these to the research team; and will be asked to comment on adaptations in the staff interviews). Other service-related aspects of implementation will be captured as part of the economic evaluation (e.g., costs, non-attendance at booked sessions);e)*Maintenance* at the individual (carer) level will be evaluated through the proportion of carers completing the 6 month assessment and completing interventions. At the system level, maintenance will be determined through the CHWS being able to continue beyond its initial two year intervention period.

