#### Subsequent appointments and episode of care.

CHWS staff may schedule face-to-face, phone or online appointments with carers to follow up on aspects of interventions or activities after the first appointment, at a frequency that is mutually agreed upon between the carer and the staff member.

Carer involvement with the CHWS will last an average of 6 months (episode of care), from initial contact to final assessment, **with a standard episode of care being six months duration**, from the time of completion of the initial assessments. The decision regarding discharge timing will be made by the CHWS Primary contact staff member and the carer.

Although it is anticipated that the standard episode of care will be six months, carers with ongoing needs being actively addressed by the CHWS or who have added one or more extra interventions during the 6 month period may opt to continue with the Service beyond the 6 month mark. Those who complete an episode of care with the CHWS can be re-referred if their circumstances change, or new issues arise.

For situations where the person being cared for transitions from home to residential care (for permanent care, not for respite care), or in situations where a care-recipient passes away during the episode of care for the carer, the carer will have the option to continue with CHWS support (with review to determine if needs have changed), or to cease involvement with the CHWS (with re-assessment at this time point if this is acceptable to the carer).

The level of risk for adverse events associated with participating in the CHWS is considered low. If an adverse event occurs, it will be reported to the CHWS Manager, and then to the research team, who will inform the Ethics Committee. The health professional/s involved will provide or organise short term assistance and care as required, including supporting seeking medical support.

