### Sample size calculation

This is a pragmatic evaluation study of a new service at Peninsula Health, which will recruit for a 15 month period, with six month follow-up assessments. In the first 10 months of operation, the CHWS will operate one day/week, and for the subsequent five months, two days/week (to allow time for growth in referral base). Conservatively, we estimate two new referrals/ week on average for the first 5 months of CHWS operations, 4/week for months 6–10, and then for the final five months of recruitment (with the CHWS operating 2 days/week) 8 referrals/week. Based on 48 weeks/year of operation, over the 1.25 years of recruitment for the study, this will mean an anticipated 248 people referred. We estimate that 55% of carers referred to attend the Service will consent to participating in the project (n = 137) and undergo assessment and intervention. A previous intervention study to support carers of older people being discharged home from hospital achieved a significant mean improvement of 0.2 on the total average item score for the primary effectiveness outcome measure in this study – the Preparedness for Caregiving Scale [34] (mean average item score at baseline = 2.67 (0.57 sd) on the 0–4 scale for each item, with a sample of n = 140 (two groups)) [36]. This sample size is also expected to be sufficient for the majority of outcome measures being collected.

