### Data analysis

Extracted data for the CHWS evaluation comparing baseline and 6 month assessment data will be analysed using parametric analyses for continuous, normally distributed data, and non-parametric analyses for categorical or non-normally distributed data. Analyses for comparison of the continuous core and additional domain assessment between initial and 6 month assessments will be performed using generalised linear regression. Analyses will be conducted on an intention-to-treat basis.

Analysis for the cost effectiveness evaluation will involve the costing of items based on actual costs where available, and where these are not available, costs, excluding carer time, will be based on market rates, with carer time based on the minimum wage. All costs will be presented as AUD 2025/26, with costs collected prior to 2025/26 to be inflated by CPI [60]. The EQ-5D-5L raw scores will be converted to a utility index using Australian weights [61], and then into QALYs. The ICER will be calculated using the bootstrap method (5,000 replications) with the results presented on a cost-effectiveness plane and as a probability of cost-effectiveness across a range of willingness to pay thresholds (AUD $0 to $50,000) [62].

For the qualitative study (semi-structured interviews) of carers and referrers, recruitment will continue until data saturation for the carers and the referrers groups. Thematic analyses will be undertaken independently by two members of the research team for each participant group, using Braun and Clarke’s six stages of reflexive thematic analysis [63]. In cases of disagreement between the coders, the two team members will discuss their perspectives to achieve agreement on themes. The thematic analyses will then be presented to a subgroup of the research team and the CHWS staff (n = 6) to review and discuss themes, for finalisation of the thematic analysis for each participant group. A similar approach will be used for analysis of the CHWS staff interviews, although the number of interviews will be small and constrained by the number of current staff, together with interviews with any staff who leave the service. Commonalities and differences in themes between the participant groups will be identified. All quotes to support themes will be de-identified.

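### Two carers of one person can both enrol and each reports that person's whole care package, so its cost change enters the cost-utility ratio twice

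*Protocol article*

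**What the plan says.** All references are to the protocol article.

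- **Who can enter (Carers).** There are three inclusion criteria: age 50 or over, living in the community, and "being an informal (unpaid) carer (as defined above) for a person aged ≥65 years living in the community". No exclusions are listed. Carers are defined in the plural, as "family members and/or friends who routinely support the older person through assistance with household tasks" or through any of several other kinds of support. Being the main, sole or co-resident carer is not required.
- **What is costed (Implementation outcomes, item b; also the health economics survey in Table 1).** The analysis takes a societal viewpoint. One cost item is "the quantity of care provided to the person requiring care". Each carer gives it in three parts: their own weekly hours, those of other unpaid helpers, and paid hours.
- **What counts as effect (same item).** The effect is the QALY change of the individual carer, from that carer's EQ-5D-5L at the first appointment and at six months.
- **How the ratio is estimated (Data analysis).** "The ICER will be calculated using the bootstrap method (5,000 replications"; the unit to be resampled is not named.
- **How records reach the analysts (Data collection and statistical analyses).** The health service's intake team extracts de-identified data for consenting carers, using each carer's own identifier. No identifier for the care recipient is mentioned.

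**The concern.** The cost item and the effect have different units. Hours of care describe the recipient: own, other unpaid and paid hours together make up everything that person receives. The QALY belongs to the carer. With one enrolled carer per recipient this does no harm. With two, the first carer's own hours reappear as other unpaid hours in the second carer's survey, the reverse also holds, and the paid hours appear in both. Society bears the change in that person's care once, but the numerator of the ICER receives it twice.

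The survey itself expects recipients to have more than one unpaid carer, since it asks about the hours of others. A spouse and an adult child aged 50 or over, or two siblings, would both qualify.

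The error can go either way. If care hours fall, the saving is exaggerated; if they rise, the added cost is. Service costs, the carer's own hospital use and the carer's leisure hours are not affected, because they do belong to each carer. Nor does the double count touch the Preparedness for Caregiving Scale, the primary effectiveness outcome.

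**Working it through.** **Inputs.** The target number of carers, N = 137, comes from Sample size calculation. It reproduces from the stated inputs: 0.55 × 248 = 136.4, given as 137. This point disputes no stated figure. The share s of enrolled carers who belong to a same-recipient pair is not in the article, so a range of 2% to 20% is assumed.

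**Step 1: one pair, with illustrative weekly hours (assumed).** Carer A goes from 30 to 24, carer B from 10 to 8, and paid care from 5 to 9.

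| Source | Own | Other unpaid | Paid | Total change |
|---|---|---|---|---|
| True change for the recipient | – | – | – | −6 − 2 + 4 = −4 |
| A's survey | −6 | −2 | +4 | −4 |
| B's survey | −2 | −6 | +4 | −4 |
| Sum entering the analysis | | | | −8 |

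The recorded change is exactly twice the true change, and it is set against two separate QALY changes.

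**Step 2: the whole sample.** Let d be the mean care-cost change per recipient, taken as equal for paired and unpaired recipients.

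- Distinct recipients = N(1 − s/2)
- True total = N(1 − s/2)d
- Recorded total = Nd
- Overstatement = 1/(1 − s/2) − 1

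| s (assumed) | Pairs, 137s/2 | Distinct recipients | Overstatement of care-cost component |
|---|---|---|---|
| 2% | 1.4 | 135.6 | 1/0.990 − 1 = 1.0% |
| 5% | 3.4 | 133.6 | 1/0.975 − 1 = 2.6% |
| 10% | 6.9 | 130.2 | 1/0.950 − 1 = 5.3% |
| 20% | 13.7 | 123.3 | 1/0.900 − 1 = 11.1% |

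**Step 3: precision.** The two surveys of a pair describe the same quantity. If carers are resampled as if independent, the standard error of this component is too small by a factor of at most √(1 + s), reached when the two reports agree perfectly: 1.010, 1.025, 1.049 and 1.095 for the four shares. This is secondary to the double count.

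**Limits of the arithmetic.** The doubling is exact in hours if both carers report accurately over the same calendar period; staggered entry would make it approximate. It is exact in money if own and other unpaid hours carry the same hourly value. Data analysis values carer time at the minimum wage and does not say whether that covers the time of other unpaid people.

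**The case against.** The strongest reply is that nothing in the article is contradicted. A condensed article commonly leaves record linkage, the bootstrap unit and costing rules to a full protocol or analysis plan, and neither is shown. How often pairs enrol is unknown, and at shares of 2% to 10% the error is only about 1% to 5% of one cost component.

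Much of this stands. The unnamed resampling unit would be no finding alone, and the size is modest. But the article does fix who may enrol, what each carer reports and whose QALY counts, and the mismatch follows from those three statements. A later plan can repair it only if carers of one person can be linked. The data flow described extracts each carer's record under that carer's own identifier and then de-identifies it, so the link has to be captured before that step. The full screening questionnaire, which is not shown, may already ask for it.

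A reader might infer three stronger points that the article does not support.

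- **Returning carers contaminating the baseline.** The article says "Those who complete an episode of care with the CHWS can be re-referred if their circumstances change, or new issues arise". That is re-referral to the service. Nowhere is a returning carer said to re-enter the research. Both cost windows are tied to the carer's first appointment, research involvement is described as one baseline and one six-month assessment, and extraction is by a unique carer identifier. The natural reading is one record per carer.
- **Reach inflated by counting referrals as people.** The phrase "this will mean an anticipated 248 people referred" is a planning forecast. The targets set for reach are use of appointment slots and sample size against plan. A slot used by a returning carer is still a used slot.
- **A dollar shift in the ICER.** Any figure per QALY needs an assumed change in hours, an hourly rate and a QALY gain as well as s. The article supplies none of these values.

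**Conclusion.** The point holds for co-enrolled carers. As written, the plan lets two carers of one person enter and counts the change in that person's care cost once for each of them. The care-cost component is overstated by 1/(1 − s/2) − 1, which is 1.0% to 11.1% for s from 2% to 20%. This rests on an assumed s, pairs rather than larger groups, and equal mean change in paired and unpaired recipients. If no recipient has two enrolled carers, the error is zero. The direction of the effect on the ICER depends on whether care costs rise or fall, and its size cannot be derived from the article. It is a modest bias in the economic analysis that is worth removing because removal is cheap. It does not threaten the primary effectiveness outcome.

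**What to change.** 1. **Capture the link.** In the initial telephone screening questionnaire (Carers), ask whether another enrolled carer supports the same person, and assign a recipient code. For carers already recruited, the intake team can make the same check at extraction, before de-identification (Data collection and statistical analyses). The analysts need only the code, not the recipient's identity.
2. **Cost each care package once.** In Implementation outcomes, item b, and in Data analysis, state that a recipient's care hours count once, for example by dividing them equally among that recipient's enrolled carers. In the illustrative pair each carer would then contribute −2 hours, giving the true −4. If the two reports differ, giving each carer half of their own reported total amounts to averaging the reports.
3. **Resample by recipient.** State that the 5,000 bootstrap replications draw recipients, with all their enrolled carers, rather than individual carers.
4. **Report the count.** Give the number of recipients with more than one enrolled carer, so that readers can see whether the issue arose.

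The cost is one screening item or one extraction check, a few sentences of wording and slightly more analysis work. Eligibility, the number of carers and the assessments stay as they are. A sentence saying that each carer contributes the first episode only would be an optional clarification.

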#### CHWS staff.

Staffing of the CHWS includes a social worker, a psychologist, a physiotherapist, and an occupational therapist, all with experience working with older people, and their carers. Initial staffing for the clinical psychologist and the social worker will be one day/week; while the physiotherapist and occupational therapist will work 1/2 day/week. Staffing levels (time) will be doubled in the second year of the CHWS operations (2025). In the last three months of recruitment, all CHWS staff will be invited to participate in an interview as part of the service evaluation. Staff will be informed that participation in the interview will be voluntary and that their decision to participate in the interview or not will not affect their employment with the CHWS. Staff willing to be interviewed will provide written informed consent. As part of ensuring the new Service is responsive to issues identified as it becomes more established, there will also be opportunities for meetings between the researchers and the CHWS staff intermittently to discuss CHWS operations and potential areas for clarifying or modifying aspects of the Service.

